#### Inclusion criteria

2.2.2

(1)Those who meet the ACI diagnostic criteria for Western medicine;(2)Those who meet the diagnostic criteria for stroke in Chinese medicine;(3)The time from onset to admission for treatment is within 72 hours;(4)The National Institutes of Health Stroke Scale (NIHSS) score is ≥6 points and ≤22 points;(5)Patients with first onset of ACI or patients with recurrent stroke have fully recovered before the onset of this disease;(6)Those who voluntarily accept the clinical observation of this project and sign the informed consent;

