In terms of treatment, Western medicine has a greater limitation in the treatment of cerebral infarction.^[5]^ Western medicine treatment of cerebral infarction is mainly based on thrombolysis, antiplatelet aggregation drugs, and scavenging oxygen free radicals. The use of anti-platelet aggregation drugs is prone to bleeding, gastrointestinal reactions, liver and kidney damage, and is not suitable for patients to take for a long time. In addition, for the treatment of ACI, clinically, intravenous thrombolysis is often used to treat the disease.^[6]^ However, most patients have missed the thrombolytic time window when they were admitted to the hospital, or are unable to take thrombolytic therapy because of the uncertain onset time. With the continuous development of imaging diagnosis technology and equipment, the current ultra-early cerebral infarction diagnosis technology solutions available for clinical use are no longer limited to conventional computed tomography (CT) plain scans, and more and more new technical methods are being developed and utilized photon emission tomography, positron emission tomography, etc.^[7]^ However, the above-mentioned new diagnostic technology has not been popularized in primary medical institutions, and the medical burden is too heavy and the operation time is too long. The inability to complete the assessment of cerebral blood flow in emergency patients in a short time has become a difficult bottleneck for the development of this disease.^[8,9]^ Studies have found that CT perfusion imaging (CTPI) can detect abnormal brain tissue perfusion 30 minutes after the onset of cerebral ischemia, providing the earliest and most valuable information for clinical diagnosis and treatment. In recent years, the effect of traditional Chinese medicine (TCM) on ACI has been remarkable. Therefore, this study intends to use a clinical randomized controlled study to explore the exact effect of TCM in the treatment of acute cerebral infarction, and use CTPI imaging methods to evaluate the effect.

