### Study design and settings

2.1

A brief flowchart of the entire study is shown in Figure 1. We will perform a 2-group, randomized, single-blind, placebo-controlled, and multi-center trial that will evaluate the efficacy and safety of TCM cooperative therapy for patients with ACI. This study will use a completely random grouping and parallel control observation design method. We will ensure the balance of the baseline data of the two groups through a sufficient sample size and a completely randomized grouping method. The protocol includes elements recommended in the Standard Protocol Items: Recommendations for Interventional Trials checklist (Additional file 1).

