### Participants

2.2

All cases will be included in patients with acute stage of cerebral infarction admitted to the Department of Neurology, Dongzhimen Hospital. CTPI examination of the head will be completed. They will be randomly divided into two groups, the intervention group and the control group.

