#### Exclusion criteria

2.2.3

Patients will be excluded if they meet the following criteria:

(1)Large-scale cerebral infarction, the vital signs are not stable;(2)Transient ischemic attack or cerebral hemorrhage;(3)With severe heart, liver, lung, kidney, and hematopoietic system diseases;(4)Pregnancy or lactation period;(5)Mental abnormalities and the patient who cannot cooperate.

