#### Different interventions given in two groups

2.3.1

The control group will be given basic Western medicine treatment. The course of treatment was 2 weeks, and the effect was observed after 2 weeks. Followed up to 3 months after onset. We will refer to the “Chinese Guidelines for the Diagnosis and Treatment of Acute Ischemic Stroke 2018 Edition” for the treatment of cerebral infarction formulated by the Chinese Medical Association Neurology Branch. Specific plans are: aspirin 100 mg, clopidogrel hydrogen sulfate 75 mg, orally once a day before bedtime; and routine nutritional nerves, lowering fat density, and improving microcirculation treatment for patients with acute stage of cerebral infarction; related to other diseases Specialist treatment, but it should be noted whether the medication affects the effect of the test drug and recorded in detail. The intervention group will be given TCM cooperative therapy. In addition, the two groups will be given basic Western medicine treatment at the same time. If there are hypertension, coronary heart disease, diabetes, infection, electrolyte disturbance and other symptoms, we will give routine treatment and symptomatic treatment.

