#### Primary outcome measures

2.4.1

The primary outcome measure will be evaluated using CT imaging parameters. Brain CTPI parameters collection method: Siemens dual-source CT *(Device model: Somatom Definition Flash, device number: 73396),* CTPI imaging examination of patients with unknown onset time. The opposing areas of the cerebral hemispheres on both sides are measured to quickly determine if there is a reversible ischemic zone. Using a high-pressure syringe, a nonionic contrast agent is injected into the patient's anterior cubital vein. Then, a single layer of continuous dynamic scanning is performed on the selected layer. The resulting image is processed by Siemens CTPI software package for subsequent processing. We will use the midline of the brain as the mirror to select the area of interest, and measure the lesion area and the corresponding area on the opposite side symmetrically. We will use this method to obtain cerebral blood flow (CBF), cerebral blood volume (CBV), and mean transit time (MTT) at different levels on both sides of the brain.

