## Discussion

3

The early diagnosis of ACI is of great significance to improve the prognosis of patients and save patients’ lives.^[10]^ Because only when the condition is found and diagnosed early in the onset of cerebral infarction (within 6 hours) can subsequent treatment such as intravenous thrombolysis be advanced. In this way, we can grasp the optimal timing of thrombolysis and reduce the degree of brain tissue damage.^[11,12]^ In addition, it is clinically recognized that changes in cerebral blood flow can feed back pathological changes in human brain tissue.^[13]^ For example, cerebral hemodynamic changes in patients with cerebral infarction have obvious characteristics. It is mainly manifested in local neurochemical changes in the early stages of onset.^[14]^ In order to ensure the local normal blood supply, the cerebral blood vessels will inevitably show a state of compensatory expansion. Corresponding resistance to cerebrovascular circulation will be significantly reduced. Imaging showed increased cerebral blood flow and prolonged mean transit time of contrast medium.^[15]^ When the vasodilation reaches the upper limit, cerebral blood flow will decrease. Once the state persists for more than 6 hours, it means that the blood supply to the brain is greatly reduced. At this time, cerebrovascular dilatation reaches a decompensated state, which in turn causes irreversible damage. Some scholars have stated in research that comprehensively grasping the patient's brain imaging diagnostic information in the early stages of onset will help physicians to correctly judge the condition such as whether the central neuron is necrotic, whether there are penumbras in the surrounding area, and the area of the penumbra area is geometric.^[16,17]^ Take first aid measures symptomatically. It is not difficult to see that clarifying the lesions and their changes in cerebral blood flow is very important to reverse the outcome of brain tissue. And how to obtain more comprehensive and valuable information about blood flow in living cells has always been the focus of investigation in imaging medicine.

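### Reperfused patients are eligible, but the stated between-group test on CT perfusion has no term for reperfusion and nothing fixes it before allocation: a minor, cheaply recovered loss of precision

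*Protocol article*

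**What the plan says.** **Eligibility.** Section 2.2.2 requires that "The time from onset to admission for treatment is within 72 hours". None of its six items mentions thrombolysis, thrombectomy or recanalisation. Nor do the five exclusions in 2.2.3, the first of which is "Large-scale cerebral infarction, the vital signs are not stable".

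**Outcome.** Section 2.4.1 states: "The primary outcome measure will be evaluated using CT imaging parameters". The parameters named there are CBF, CBV and MTT.

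**Allocation and balance.** Section 2.1 relies on chance alone: "We will ensure the balance of the baseline data of the two groups through a sufficient sample size and a completely randomized grouping method". Section 2.2 says "CTPI examination of the head will be completed" and then describes random division into the two groups. Section 2.6 assigns patients by sealed envelope in order of inclusion. Neither section says whether the decision on reperfusion comes before or after the envelope is opened.

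**Analysis.** Section 2.7 names one-way analysis of variance for comparing the groups, paired t tests for change within a group, and a two-sided 0.05 level.

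**How common reperfusion is likely to be.** The Introduction counts thrombolysis among the main Western treatments but says that "most patients have missed the thrombolytic time window when they were admitted to the hospital". The Discussion ties thrombolysis to diagnosis in the first 6 hours. The background regimen in 2.3.1 reads "Specific plans are: aspirin 100 mg, clopidogrel hydrogen sulfate 75 mg, orally once a day before bedtime", followed by supportive measures. It neither lists thrombolysis nor forbids it.

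**The concern.** A 72-hour window includes the first hours, when thrombolysis is possible, so some enrolled patients may be reperfused. Reopening a vessel changes blood flow, which is what the primary outcome measures. A one-factor test leaves that variation in the residual, and a completely random allocation leaves the split between the arms to chance. Both reduce the precision of the TCM comparison.

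The second part is timing. Reperfusion can be used safely as an adjustment factor only if it is settled before allocation, and the article does not ensure that. Without a rule on sequence, a later analysis that added the factor could be adjusting for something that happened after randomisation.

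**Working it through.** The article states no sample size, power, effect size, SD or reperfusion rate, so there is no figure of the plan's own to reproduce. Everything below is an illustration on assumed inputs.

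**Inputs**
- Two-sided level 0.05 (2.7), so z = 1.960.
- Nominal power 80% when reperfusion plays no part (assumed), so z = 0.842 and the sum is 2.802.
- Outcome SD of 1 among patients with the same reperfusion status (assumed).
- Share reperfused, p: 5%, 8.3%, 10% and 20% (assumed). The 8.3% is 6/72, the share arriving in the first 6 hours if arrivals were spread evenly over the window.
- Shift in the outcome from reperfusion, d: 0.5 or 1 SD (assumed).

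**Formulas**
- Added outcome variance: v = p(1 - p)d².
- Power of the test without the factor: Φ(2.802/√(1 + v) - 1.960).

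For example, at p = 0.20 and d = 1, v = 0.20 × 0.80 × 1 = 0.16. Then 2.802/√1.16 = 2.602, 2.602 - 1.960 = 0.642, and Φ(0.642) = 0.739.

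| p | d | v | Power without the factor | Points lost from 80% |
|---|---|---|---|---|
| 5% | 0.5 | 0.012 | 79.5% | 0.5 |
| 5% | 1 | 0.048 | 78.2% | 1.8 |
| 8.3% | 0.5 | 0.019 | 79.3% | 0.7 |
| 8.3% | 1 | 0.076 | 77.1% | 2.9 |
| 10% | 0.5 | 0.0225 | 79.1% | 0.9 |
| 10% | 1 | 0.09 | 76.5% | 3.5 |
| 20% | 0.5 | 0.04 | 78.4% | 1.6 |
| 20% | 1 | 0.16 | 73.9% | 6.1 |

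**Does the factor recover the loss?** Simulation with 60 per arm (assumed), a treatment effect of 0.516 SD and 40,000 runs gave, without and then with reperfusion in the model:
- p = 8.3%, d = 1: 77.0%, then 79.7%
- p = 10%, d = 0.5: 79.4%, then 80.2%
- p = 10%, d = 1: 76.3%, then 79.7%
- p = 20%, d = 0.5: 78.3%, then 79.8%
- p = 20%, d = 1: 73.3%, then 79.4%

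**Is the stated test invalid?** No. Simulated type I error was 0.045-0.052 without the factor and 0.044-0.051 with it (20,000 runs). A separate simulation at p = 20%, d = 0.8 with 20, 30 and 60 per arm gave 0.049-0.051, and the mean group difference was within about 0.002 SD of zero.

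**Chance imbalance.** With 60 per arm, the probability that the arms differ by 6 or more reperfused patients (10 percentage points) is 0.068 at p = 8.3%, 0.093 at 10% and 0.208 at 20%. This is already contained in v and is not a further loss.

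**What baseline perfusion would add.** Adjusting for a baseline value with correlation r to the outcome gives power Φ(2.802/√(1 - r²) - 1.960). At an assumed r = 0.5, 2.802/√0.75 = 3.235 and the power is Φ(1.275) = 0.899. That gain of about 10 points is larger than any in the table above. CT perfusion is already measured before treatment.

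**The case against.** The strongest reply is that this concerns a covariate, and covariates are commonly left to an analysis plan. Enrolling patients on guideline care in both arms is ordinary add-on design, and an unadjusted randomised comparison is not an error. The text itself points to low use, and every input to the calculation is assumed. Reperfusion is also only one prognostic factor among several, and baseline perfusion would recover more.

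Much of this stands. It is why the point is minor, and why the remedy should include baseline perfusion. It does not dispose of the point. The article prints full eligibility lists and names a specific one-factor test, so the comment addresses what the document fixes. An analysis plan could add a term, but it could not settle the order of reperfusion and allocation once patients have been enrolled.

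A reader might go further and infer any of the following, none of which the article supports:
- *That reperfusion biases the TCM comparison.* Randomisation protects it, and the simulated type I error stays near 0.05.
- *That reperfusion will differ by arm because clinicians know the allocation.* The silence on sequence leaves this possible, but nothing in the article shows it.
- *That reperfused patients must be excluded.* Admitting them is a legitimate choice, and adjustment is enough.

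The paired tests in 2.7 cannot isolate TCM whether or not anyone is reperfused, because natural course and background treatment change perfusion within each arm. That is a separate matter and adds no weight here.

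**Conclusion.** The point holds as a minor one. Reperfused patients can enter, the outcome is one that reperfusion acts on, and the stated test takes no account of it. The comparison remains valid; the consequence is a small loss of precision. At the low use that the article suggests (5-8% assumed), the loss is about 0.5-3 points from a nominal 80% power. The figure of about 6 points needs 20% use together with a full 1 SD shift, which fits poorly with the statement that most patients arrive too late for thrombolysis. The nominal 80%, the rates, the shifts and the 60 per arm are all assumptions. What the article does establish is that no rule makes reperfusion a pre-randomisation factor, and that the group comparison uses neither it nor the baseline scan.

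**What to change.** **In 2.6, add:** The envelope is opened only after the decision on reperfusion treatment has been made and any such treatment has been given under usual care. Reperfusion (yes/no) is recorded before the envelope is opened.

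**In 2.7, replace the one-way analysis of variance with:** The groups are compared by an ANCOVA containing treatment group, the baseline value of the outcome and pre-randomisation reperfusion (yes/no). Conclusions about TCM rest on this between-group comparison.

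The order matters: the sentence in 2.6 is what makes the reperfusion term in 2.7 safe to use.

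**Cost.** One extra case report form item, one sentence on sequence and a changed model, with no extra scan and no change to who is eligible. The downside is slightly later randomisation for early arrivals. Section 3.1 says recruitment had not started at submission, so on that status the change could be made before the first patient is enrolled.

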#### Exclusion criteria

2.2.3

Patients will be excluded if they meet the following criteria:

(1)Large-scale cerebral infarction, the vital signs are not stable;(2)Transient ischemic attack or cerebral hemorrhage;(3)With severe heart, liver, lung, kidney, and hematopoietic system diseases;(4)Pregnancy or lactation period;(5)Mental abnormalities and the patient who cannot cooperate.

#### Case rejection or shedding criteria

2.2.4

(1)Allergic reactions or serious adverse events occur.(2)In the course of clinical observation, the patient developed other diseases and did not meet the inclusion criteria.(3)Subjects have poor compliance (compliance with test drugs <80% or> 120%), or change medications automatically.(4)Cases in which blindness is disrupted midway for various reasons.(5)Patients and their families resolutely terminate the experiment.

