#### Suspension criteria

2.2.5

(1)In the treatment of this study, the patient was unexpectedly pregnant or had serious adverse reactions, and it was difficult to continue to receive treatment.(2)During the implementation of this study, there was an obvious exacerbation or complications.(Fig. 2)

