#### Safety observation measures

2.4.3

(1)General physical examination items, such as body temperature, heart rate, respiration, blood pressure, and blood sugar.(2)Possible adverse events and the incidence of adverse events.

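### Section 2.2.4 lets randomised patients be rejected for allergy, serious adverse events, new disease, poor test-drug compliance or self-made medication changes, and nothing keeps them in follow-up or analysis

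*Protocol article*

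**What the plan says.** Section 2.2.4 of the protocol article gives five grounds for rejection or shedding of a case. Three concern us:

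- harm: "Allergic reactions or serious adverse events occur";
- new illness during observation: "the patient developed other diseases and did not meet the inclusion criteria";
- drug taking: "Subjects have poor compliance (compliance with test drugs <80% or> 120%), or change medications automatically".

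The other two are broken blinding and termination by the patient or family.

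Section 2.2.5 separately lists suspension criteria. One covers patients who "had serious adverse reactions, and it was difficult to continue to receive treatment". Another reads "During the implementation of this study, there was an obvious exacerbation or complications".

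On the arms, section 2.3.1 says "The control group will be given basic Western medicine treatment" and "The intervention group will be given TCM cooperative therapy", with the basic Western treatment common to both. It describes no placebo. Section 2.1 nevertheless labels the trial placebo-controlled and single-blind, and section 2.6 distributes numbered drugs with emergency letters.

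The safety outcomes in section 2.4.3 include "Possible adverse events and the incidence of adverse events". Section 2.7 names tests at a two-sided 5% level. No section says what happens to the follow-up or the data of a rejected case.

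**The concern.** Randomisation makes the two arms comparable at entry. A rule that removes patients for what happens to them afterwards can undo this if the removal depends on treatment and on how the patient fares. Allergy, serious adverse events, new disease, poor compliance and medication changes can all depend on both. If the arms lose different numbers or different kinds of patients, those who remain can differ without any treatment effect.

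Two results are at stake. For CT perfusion (CTPI), NIHSS and the Barthel Index (BI), patients doing badly could drop out of the comparison, and more of them from one arm than the other. For safety, the patients with the most important events are the ones the rule rejects.

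This is not a complaint that an analysis population is undefined, which could be left to an analysis plan. The article states a rejection rule, and applying it as written gives a worse result than having no such rule.

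**Working it through.** **Figures in the article.** It gives no sample size, power, effect size, SD or dropout rate, so there is no stated figure to reproduce. The text was checked first. The arithmetic after it is illustration on assumed inputs.

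**Step 1: what rejection means.** Suspension has its own section (2.2.5), which speaks of difficulty in continuing treatment. Section 2.2.4 stands apart from it and speaks of rejecting the case. The natural reading of 2.2.4 is therefore removal of the case, although the article does not spell out the consequence.

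**Step 2: where the grounds fall.** By section 2.3.1 the arms differ only by the added TCM, with no placebo described. On that description, compliance with test drugs and allergy to them bear mainly on the intervention arm. Serious adverse events, new disease and medication changes can occur in either arm.

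**Step 3: safety.** If every patient with an allergic reaction or serious adverse event leaves the data, the incidence of these events among those retained is 0% in both arms, whatever the true rates.

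**Step 4: size on assumed rates.** Assume no true effect, 100 randomised per arm, an outcome SD of 1, a share eI rejected in the intervention arm and eC = 5% in control. The standard error is SE = √(1/[100(1 − eI)] + 1/[100(1 − eC)]). The type I error is 1 − Φ(1.96 − b/SE) + Φ(−1.96 − b/SE), where b is the bias in SD units.

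*Model A.* Rejected patients are g SD worse than retained ones, so b = (eI − eC)·g. Example with eI = 20% and g = 1: b = 0.15 and SE = √(1/80 + 1/95) = 0.152, so b/SE = 0.99 and the type I error is 16.7%.

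*Model B.* Rejection takes the lowest fraction p of a normal variable that correlates ρ with outcome. The retained mean shifts by ρ·φ(z_p)/(1 − p), where φ(z_p)/(1 − p) is 0.109 at 5%, 0.195 at 10%, 0.274 at 15% and 0.350 at 20%. Example with 20% versus 5% and ρ = 1: b = 0.350 − 0.109 = 0.241, b/SE = 1.59, and the type I error is 35.6%.

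| Rejected, intervention vs control | Model A, g = 0.5 | Model A, g = 1 | Model B, ρ = 0.5 | Model B, ρ = 1 |
|---|---|---|---|---|
| 5% vs 5% | 5.0% | 5.0% | 5.0% | 5.0% |
| 10% vs 5% | 5.3% | 6.3% | 6.0% | 9.0% |
| 15% vs 5% | 6.3% | 10.3% | 8.6% | 19.9% |
| 20% vs 5% | 7.8% | 16.7% | 12.5% | 35.6% |

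The Model B figures keep the SD at 1 after removal. Allowing for the smaller variance of the retained patients raises the 15% and 20% rows to 8.9% and 13.2% at ρ = 0.5, and to 25.8% and 48.4% at ρ = 1. The case ρ = 1, where exactly the worst outcomes are rejected, is an extreme.

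**Step 5: after the fix.** With all randomised patients kept in their arm and their outcomes obtained, b = 0 and the type I error is 5%.

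**The case against.** The strongest reply is that removal from analysis is an inference. Section 2.2.4 states no analytic consequence, its list includes ordinary withdrawal by the patient or family, and who is analysed is commonly settled in a fuller document. This stands in part: the word may have been meant as withdrawal from treatment. But the text speaks of rejecting the case, and nothing in the article offsets it.

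A reader might also infer several stronger things that the article does not support:

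- *That worsening patients in 2.2.5 are dropped.* That section reads as stopping treatment, and nothing in it says their data are discarded.
- *That the compliance rule can reject patients in one arm only.* Section 2.3.1 suggests so, but the placebo-controlled label in 2.1 and the numbered drugs in 2.6 leave room for test drugs in both arms. These sections must be reconciled.
- *That every ground is related to outcome or treatment.* Broken blinding and family withdrawal need not be.
- *That the direction of bias is certain.* Both arms receive the same background drugs and can have serious events. If TCM prevented poor courses, rejecting them would take more patients from control and work against TCM.
- *That 2.2.4 flatly contradicts 2.4.3.* An event can be recorded and counted before the patient leaves. The two conflict only if rejected cases also leave the safety data.

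**Conclusion.** The point holds in limited form. Section 2.2.4 states post-randomisation rejection on grounds related to outcome or treatment, and no section keeps those patients in follow-up or analysis. Applied as written, it breaks the randomised comparison and can strip the safety outcome of its serious events. On the arms as section 2.3.1 describes them, the likely bias favours TCM, but that is an expectation and not something the article lets one derive.

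The size is unknown. With 10% to 20% versus 5% rejected and 100 per arm, all assumed, the type I error runs from about 5%, where rejection is only weakly tied to outcome, to well above 20%, where it takes the worst outcomes. It stays at 5% if rejection is equal in rate and severity. Because the defect lies in a stated rule and recruitment has not begun, it should be corrected before the trial starts.

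**What to change.** Add to the protocol that:

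1. section 2.2.4, and for clarity 2.2.5, governs study treatment only;
2. every randomised patient stays in follow-up at 2 weeks and 3 months and is analysed in the assigned arm for CTPI, NIHSS and BI;
3. all adverse events in all treated patients are counted for 2.4.3, including those that led to stopping treatment;
4. the set with 80% to 120% compliance is a labelled sensitivity analysis.

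Reconcile sections 2.1, 2.3.1 and 2.6 on whether the control arm receives a test drug, so that it is clear to whom the compliance rule applies. The clinical criteria for stopping treatment do not change.

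The cost is protocol wording, continued visits for patients who stop treatment, and a possibly diluted effect estimate. The bias is removed only to the extent that outcomes are actually obtained, so patients who refuse further follow-up remain a residual problem. If the sponsor already meant withdrawal from treatment only, the change is one of wording.
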